**Figure 1 F1:**
[figure not shown]
Summary of intervention and standard care access to thrombectomy treatment for the ‘target’ population. ^∗^Any intervention group patients who are not redirected will undergo usual care assessment on arrival at the local Primary Stroke Centre and may still receive thrombectomy through the standard secondary transfer route.

### Implementation of the study intervention and control

#### Implementation for ambulance practitioners

Any grade of ambulance practitioner based within a randomised station/team that would normally attempt to identify suspected stroke is involved in the study.

When the study launches in each region, intervention ambulance practitioners are provided with information about the trial including pocket-sized cards covering pathway initiation criteria and specific contact details for the participating CSC team. The pathway was purposely designed to use routinely available information and as such negate a need for trial-specific training. Practitioners are instructed to start using the intervention pathway on a specific date in synchronisation with the receiving CSC.

Ambulance practitioners based within standard care stations are informed that a study about thrombectomy is taking place and routinely recorded data will be used, but otherwise instructed to continue with standard care pathways.

As double-crewed ambulances are typically dispatched to suspected stroke patients, it is expected that two ambulance practitioners will attend most incidents. Whilst typically this should be two practitioners from the same station/team and therefore the same randomisation allocation, there may be occasions when this is not the case and both an intervention and a control practitioner are in attendance. In this latter situation, the patient is considered allocated to the intervention group and the ambulance practitioners have been advised that the intervention pathway should take precedent.

During the duration of the trial, it is anticipated that the ambulance practitioner workforce within each region will be subject to change, ie, some practitioners will leave the service and new employees will commence. Because the study population comprises all suspected and confirmed strokes seen by randomised ambulance practitioners across a participating region, newly employed ambulance practitioners will become involved in the study when they commence their employment. If practitioners employed after study launch were excluded from involvement, the study population would be incomplete. New employees will be provided with details about the study in keeping with their allocated station.

It is also anticipated that some ambulance practitioners will move station bases during the trial because of regional ambulance service workforce management decisions. In order to maintain the integrity of the trial, all ambulance practitioners will be instructed that they retain their original randomisation allocation irrespective of any operational station moves, ie, retain either the group of their station at study launch or the group of their station at commencement of new employment.

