### Cluster randomisation

Within each ambulance service region, stations/teams were eligible for randomisation if the ambulance practitioners attend incidents in geographical areas where suspected stroke patients are usually conveyed to a PSC which makes thrombectomy referrals to the participating CSC. In addition, stations/teams which usually convey directly to the participating CSC were also randomised so that all stations/teams across a region were included. This choice of all stations/teams (ambulance practitioners) across a region was because (1) ambulance practitioners and vehicles are often moved around according to operational service demand and can serve both PSCs and CSCs irrespective of station base/team, hence this approach ensures that all pathway eligible patients will be attended by a randomised ambulance practitioner and (2) the full study population can be identified (see also Study population, below).

Stations within an ambulance service region were only excluded from randomisation if they had a non-routine function and staff would not be deployed to suspected stroke incidents (eg, the station is the base for Hazardous Area Response Team practitioners only), or, if they were in geographical regions where it would be very unlikely that attended patients would be conveyed to a study relevant PSC or CSC. For example, some ambulance service regions serve more than one CSC and staff from specific stations were highly likely to only attend incidents where conveyance was to a PSC which refers to the non-study CSC.

Within each participating region, included stations/teams were allocated 1:1 between intervention and standard care using covariate constrained randomisation,^23^ balanced according to size (defined as total number of staff) and distance from the CSC. Balancing on these variables was to ensure that intervention and standard pathway ambulance practitioners were approximately equally matched in terms of important operational characteristics. For participating regions with more than one included CSC, randomisation was stratified by centre, or centre was used as a covariate in the balance metric, depending on the number of ambulance stations involved.

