#### Assignment of randomisation group

All patients will be assigned to a randomisation group according to the allocation of the attending ambulance practitioner. The ambulance data exports contain information on attending practitioners and/or stations/teams such that randomisation group can be assigned. For patients in the full study population where ambulance practitioners did not suspect stroke and this was diagnosed only after arrival at hospital, information on attending practitioners (or station/team) will be sourced in arrears from the relevant ambulance service.

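### Counting every mixed-allocation crew as intervention makes the chance of being in the intervention arm depend on crew composition as well as on randomisation

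*Protocol article*

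**What the plan says.** Stations or teams are allocated 1:1 within each region (Cluster randomisation), and each patient takes the allocation of the attending practitioner, in the singular (Assignment of randomisation group).

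Implementation for ambulance practitioners recognises that crews are usually pairs: "it is expected that two ambulance practitioners will attend most incidents". It expects that "typically this should be two practitioners from the same station/team and therefore the same randomisation allocation", but accepts that "there may be occasions when this is not the case and both an intervention and a control practitioner are in attendance". The rule for that case is: "In this latter situation, the patient is considered allocated to the intervention group". The crew is also told that the intervention pathway takes precedence.

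Staff who change base "retain their original randomisation allocation irrespective of any operational station moves", so two colleagues now at one base can hold different allocations. Cluster randomisation adds that "ambulance practitioners and vehicles are often moved around according to operational service demand". The ambulance exports are said to contain "information on attending practitioners and/or stations/teams such that randomisation group can be assigned".

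The article gives no frequency for mixed crews and no separate handling of them in the analysis.

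**The concern.** Under 1:1 cluster allocation, a patient's arm should depend only on the random draw. Under this rule it also depends on how many differently randomised stations are represented in the crew, because one intervention practitioner is enough to make the patient intervention. If crews drawn from two stations tend to attend patients who differ in location, timing or severity, that difference becomes associated with arm. The Blinding section relies on cluster allocation to rule out selection, but it does not consider crew composition.

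The secondary ITT comparison carries the imbalance in full. The primary analysis does not remove it: intervention patients without pathway contact are dropped, but mixed-crew patients with contact stay in, and none can enter control.

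A second, smaller matter concerns movers. Allocation follows the practitioner, but an export that holds only the station cannot show that a practitioner brought a different allocation from elsewhere. If it lists one station per incident, it cannot show a mixed crew either.

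**Working it through.** **The plan's own figures.** Inputs from Sample size: 150 clusters allocated 1:1 and ICC 0.01. For time, a 30-minute difference, SD 120, one-sided 5% and 90% power. For rate, 13.2% v 21.6%, two-sided 5% and 90% power. The unadjusted totals are 548.1 (time) and 852 (rate). Solving N = unadjusted total × [1 + (N/150 − 1) × 0.01] gives 563.2, so 564 (stated 564), and 894.3 (stated 894). Both reproduce, so the point is not about the sample size.

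**Chance of being in the intervention arm.** With one allocated station it is 0.50. With two, a patient is control only if both stations are control: 1 − 0.5 × 0.5 = 0.75. Drawing two stations from 150, of which 75 are intervention, gives 1 − (75/150)(74/149) = 0.752. What counts is the allocation each practitioner carries, not the present base.

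**Composition of the arms.** Let q be the share of incidents attended by practitioners from two allocated stations. The article does not give q, so it is assumed here. About half of these crews are mixed (one intervention, one control), a quarter are both intervention and a quarter both control.

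- Share of all patients in intervention: 0.5 + 0.25q
- Two-station share of the intervention arm: 0.75q / (0.5 + 0.25q)
- Two-station share of the control arm: 0.25q / (0.5 − 0.25q)

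| q (assumed) | Mixed, all incidents | Patients in intervention | Mixed, intervention arm (control 0%) | Two-station, intervention v control | Shift if two-station times differ by 30 min |
|---|---|---|---|---|---|
| 5% | 2.5% | 51.3% | 4.9% | 7.3% v 2.6% | 1.4 min |
| 10% | 5% | 52.5% | 9.5% | 14.3% v 5.3% | 2.7 min |
| 20% | 10% | 55.0% | 18.2% | 27.3% v 11.1% | 4.8 min |
| 40% | 20% | 60.0% | 33.3% | 50.0% v 25.0% | 7.5 min |

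At q = 20%: 0.15/0.55 = 27.3%, 0.05/0.45 = 11.1%, difference 16.2 points, and 0.162 × 30 = 4.8 minutes. The 30-minute difference is an assumption.

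**Rate.** Assume two-station patients are 1.5 times as likely to be treated and the overall rate is 13.2%.

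- q = 20%: the one-station rate is 13.2 / (0.8 + 0.2 × 1.5) = 12.0% and the two-station rate 18.0%. The shift is 0.162 × 6.0 = 0.97, about 1.0 point.
- q = 40%: the rates are 13.2 / (0.6 + 0.4 × 1.5) = 11.0% and 16.5%. The shift is 0.25 × 5.5 = 1.4 points.

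These shifts describe the ITT comparison. They carry over to the primary analysis only if pathway initiation is equally common in one-station and two-station crews, which the article does not say.

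**Power.** With 564 patients, power for time is 0.898 at q = 20% and 0.890 at q = 40%, so the unequal split itself costs almost nothing.

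**Concordant crews.** With mixed crews set aside, the remaining two-station incidents are both-intervention and both-control in equal parts (0.25 each), so the 1:1 balance returns.

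**Movers.** If an assumed 5% of patients in each arm were put in the wrong arm, an ITT contrast would shrink by the factor 1 − 2 × 0.05 = 0.90.

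**The case against.** The rule is prespecified and does not depend on outcome. It keeps pathway-exposed patients out of control and matches the arm to what the crew was told to do. Nothing in the article links crew mixing to severity, treatment or time. Same-station crews are described as typical, so the higher values of q fit the text poorly. All of this stands, and it limits how large the problem can be said to be.

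Four stronger readings are tempting, and the document does not support them.

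- A reader might infer that no adjustment can help because control has no mixed crews. Two-control-station crews do exist in control, so adjusting, stratifying or weighting by the number of allocated stations is possible where it is recorded.
- A reader might apply the assumed outcome difference to mixed crews alone. At q = 20% that gives 0.182 × 30 = 5.5 minutes. If two-station attendance is what matters, concordant two-station crews differ as well, including those in control, and the shift is 4.8 minutes.
- A reader might extend the sum to three stations (87.5%). The text describes crews of two.
- A reader might carry the movers' dilution into the co-primary tests. The primary analysis excludes control-assigned patients in whom the pathway was used and intervention-assigned patients without contact, which removes most misassigned patients.

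It can also be said that a sensitivity analysis belongs in the statistical analysis plan. That is so, and the plan may contain one. The assignment rule, however, is fixed in this article, and it is the rule that creates the imbalance.

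**Conclusion.** The point holds as one of comparability between the arms. It concerns neither the sample-size arithmetic nor power. The 50% v 75% chance of intervention, the 3:1 split of two-station incidents and the absence of mixed-allocation crews from control all follow directly from the stated rule and 1:1 allocation.

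Whether bias results, and how much, is unknown. It requires crew mixing to be related to outcome, and it scales with a frequency the article does not give. Under the assumed inputs the shift is about 4.8 minutes and 1.0 point with 20% two-station incidents, and 7.5 minutes and 1.4 points with 40%, against design targets of 30 minutes and 8.4 points. That is enough to justify an inexpensive check, but not to conclude that the comparison is invalid.

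Misassignment of movers is possible only in services whose exports lack practitioner identity, and it would mainly dilute the secondary ITT comparison.

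**What to change.** 1. Report the number of mixed-allocation incidents by region.
2. Prespecify a repeat of the ITT analysis of both co-primary outcomes using only incidents where all attending practitioners share one allocation. Where the number of distinct allocated stations is recorded, stratifying or weighting by it is an alternative that keeps the mixed-crew patients.
3. Repeat the primary analysis on the same concordant incidents as a sensitivity check. Concordance restores 1:1 allocation for the ITT comparison only; it does not remove the primary analysis's selection on pathway initiation, and the report should say so.
4. Assign arm by practitioner identifier against the allocation list wherever the service holds it, and use station only as a flagged fallback.

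None of this changes ambulance practice or enrolment. The cost is a little more analysis and data linkage, and the loss of mixed-crew patients from the concordant analysis (10% of incidents if 20% involve two stations).

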### Blinding

Due to the nature of the study intervention, it is not possible to blind intervention ambulance practitioners or receiving hospital stroke teams. However, because the study is cluster randomised, staff cannot influence group allocation or select patients for inclusion in the trial; all patients who meet the eligibility criteria will be included and assigned to a study group based on the randomisation allocation of the attending ambulance practitioner. Patients seen by intervention group ambulance practitioners will be included in the study whether or not the intervention pathway was deployed, and whether or not thrombectomy was received.

Participating sites are asked to conceal study group information from the clinician performing thrombectomy, which should be possible because NHS neuroradiologists are not routinely involved in urgent arrival care processes. Thrombectomy treatment decisions are based on clinical details conveyed via the hospital stroke team and brain imaging appearances. CSCs already receive patients from outside their immediate area through standard (secondary transfer) care and therefore information about a patient’s original locality would not by itself cause unblinding.

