As a research project, it is not possible to take advantage of systems used to enforce clinically adopted pathways across a large dispersed ambulance workforce such as mandatory audit, staff training and regular feedback. Instead, research relies on softer approaches for engagement such as regular communication and attempting to maintain a positive research culture. Ambulance assessed patients meeting the pathway criteria do not occur frequently for individual practitioners. It is estimated that an average of 1–2 suspected stroke patients per month are assessed by an individual practitioner, but only every 4–6 months will one of these patients fulfil the pathway initiation criteria. Therefore, individual practitioners are required to recognise an infrequent event under time pressure in the uncontrolled prehospital environment, and then remember to deploy a research intervention.

Using this described estimands intercurrent events strategy to define the intervention primary analysis group allows the impact of the pathway to be assessed without influence of an unpredictable deployment rate. This approach also makes the results more generalisable to any healthcare setting (inside and outside the UK) where any future deployment (implementation) rate may differ for different reasons.

*Control primary analysis group*: this comprises only patients where the SPEEDY pathway was NOT initiated. Any patients where the SPEEDY pathway was used will be excluded. This scenario, however, where the pathway is initiated by control assigned staff (in error), should be infrequent due to the cluster design.

*Analysis*: using the estimands defined groups, the co-primary outcomes of thrombectomy rate and time to thrombectomy will be examined using a two-part regression model. The model will be adjusted for predefined baseline covariates and the stratification variables of size of ambulance station and distance from a CSC.

Part 1 of the model will determine the chance of thrombectomy treatment occurring as a binary variable. Part 2 of the model will then analyse time to treatment as a continuous variable, conditional on thrombectomy having occurred.

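### Incidents attended by both allocations are all labelled intervention, so the group depends on who attends as well as on station randomisation, and no named adjustment covers this

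*Protocol article*

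**What the plan says.** The section on implementation for ambulance practitioners expects two practitioners at most incidents ("it is expected that two ambulance practitioners will attend most incidents"). It describes a shared station or team as typical, but accepts that "there may be occasions when this is not the case and both an intervention and a control practitioner are in attendance". For those incidents it sets the analysis label: "In this latter situation, the patient is considered allocated to the intervention group". It sets the care rule as well, recording that "the ambulance practitioners have been advised that the intervention pathway should take precedent".

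Two other statements make mixed attendance foreseeable. The Cluster randomisation section says that "ambulance practitioners and vehicles are often moved around according to operational service demand". The implementation section also tells practitioners that "they retain their original randomisation allocation irrespective of any operational station moves", so colleagues at one station can come to hold different allocations.

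The section on assignment of randomisation group refers to the attending practitioner in the singular and does not repeat the rule for mixed attendance. The Blinding section states that "because the study is cluster randomised, staff cannot influence group allocation or select patients for inclusion in the trial". On the model, the Primary analysis section says: "The model will be adjusted for predefined baseline covariates and the stratification variables of size of ambulance station and distance from a CSC". The composition of the attending crew is not named there, and neither the primary nor the secondary analysis section describes excluding mixed crews or analysing them separately.

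**The concern.** In a cluster trial, the ITT comparison is protected because the group label is a function of randomisation alone. Here the label is a function of randomisation and of how many stations are represented at the incident, and the second part is settled after randomisation. The rule is also one-sided: one intervention practitioner is enough to make the incident intervention, while control requires that every attender is control. Multi-station incidents therefore collect in the intervention arm even if every attender is correctly identified and the pathway does nothing.

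The imbalance becomes bias only if multi-station incidents have different outcomes. They could, for example through time of day, location or calendar period. The last of these is possible because moved staff keep their allocation, so mixed crews may become more common over an enrolment period running from November 2022 to an expected December 2025.

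Two features raise the stakes. Significance on time to thrombectomy alone is enough to declare the pathway effective. And the ITT analysis is the natural check on a primary analysis that keeps only intervention patients whose pathway was started and whose call was answered.

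**Working it through.** **Inputs from the article (Sample size).** 1:1 allocation, 150 clusters, ICC 0.01; for time, SD 120 minutes, target 30 minutes, one-sided 5%, 90% power, 564 treated patients; for rate, a baseline of 13.2% and a primary analysis population of 2600 to 4300, midpoint 3450.

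**Assumed, because the article gives no figure.** The share f of incidents attended from two different stations (2% to 40%), and the outcome gap between two-station and other incidents (30 minutes; 6 percentage points for rate).

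**Reproducing the plan's figure.** Unclustered total = 4 × (120 × (1.645 + 1.282) / 30)² = 548.1. With design effect 1 + (N/150 − 1) × 0.01, N = 548.1 × 0.99 / (1 − 548.1 × 0.01/150) = 563.2, against 564 stated. The sample size is sound and is not in question.

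**Probability of the intervention label.** With k independently allocated stations attending, P = 1 − 0.5^k: 0.50 for one, 0.75 for two, 0.875 for three. Constrained randomisation within regions makes these approximate.

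**Composition of the arms.** P(I) = 0.5(1 − f) + 0.75f. The two-station share is 0.75f / P(I) in intervention and 0.25f / (1 − P(I)) in control.

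**Spurious time difference under the null** = difference in shares × 30 minutes. The standard error is 120 × √(1.0276 × (1/n₁ + 1/n₀)), where 1.0276 = 1 + (564/150 − 1) × 0.01 and n₁, n₀ split 564 by P(I). It is 10.2 to 10.5 minutes. One-sided error = Φ(bias/SE − 1.645).

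| f | Arms (%) | Two-station share, intervention v control | Spurious gain | One-sided error |
|---|---|---|---|---|
| 2% | 50.5 : 49.5 | 3.0% v 1.0% | 0.6 min | 5.6% |
| 5% | 51.3 : 48.8 | 7.3% v 2.6% | 1.4 min | 6.6% |
| 20% | 55 : 45 | 27.3% v 11.1% | 4.8 min | 12% |
| 40% | 60 : 40 | 50% v 25% | 7.5 min | 18% |

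Half of two-station incidents are mixed in allocation, so these rows correspond to 1%, 2.5%, 10% and 20% mixed incidents. If two-station incidents are 30 minutes slower, the sign reverses: at f = 20% the one-sided error falls to Φ(−4.85/10.3 − 1.645) = 1.7%.

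**Rate, taken by itself.** With N = 3450, design effect 1 + (23 − 1) × 0.01 = 1.22 and SE about 1.27 points, a 6-point gap gives +0.29 points and a two-sided error of 5.6% at f = 5%, and +1.0 point and 12% at f = 20%.

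**Power.** The unequal arms cost almost nothing: power for time is about 89% at f = 40%.

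**Does the proposed adjustment work?** A null simulation of the ITT comparison used 150 stations, N = 3450, 30% of incidents with a second randomly drawn station, and rates of 19% v 10.7%. The label as written gave a mean difference of about +1.8 points. Adding an indicator for two stations brought it to within 0.1 point of zero with essentially the same SD (about 1.2 points). Restricting to same-allocation incidents also brought it to within 0.1 point of zero, with a slightly larger SD. The reason is simple: given the number of stations attending, the label depends only on the station randomisation.

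**The case against.** The article calls same-station crews typical and mixed attendance occasional, which fits the upper rows of the table best; there the error is 5.6% to 6.6%, close to nominal. This stands, and it is why the low range belongs beside the high one.

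No outcome gap, and no direction for it, is documented. Crew pairing set by a rota before the patient is seen need not be linked to severity, and the clinical, time-window and area criteria of the primary analysis population narrow the differences further. The statement about staff and vehicles moving concerns their serving both types of centre and does not itself say that crews are mixed. All of this stands against any claim of demonstrated bias. None of it restores the guarantee that the arms are comparable by design.

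The table describes an ITT comparison. The primary intervention group is restricted to started and answered calls, so the mixed-crew share there may differ. This stands.

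The detailed analysis is left to the statistical analysis plan, and the unnamed baseline covariates could include crew composition. That is possible, but the labelling rule and the assurance under Blinding are fixed in the article itself, and the two named covariates, station size and distance, do not address the issue.

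A reader might also infer that staff can steer patients into a group. The documents do not support that. Crew mix affecting the label is not evidence of anyone choosing it; the assurance under Blinding is incomplete because it omits the dependence on who attends.

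**Conclusion.** The mechanism is certain: it follows from the stated rule and 1:1 allocation, and it applies to the ITT analysis as well as the primary one. Its size is not known. Over assumed two-station shares of 2% to 40% and an assumed favourable gap of 30 minutes, the spurious time gain runs from 0.6 to 7.5 minutes against a 30-minute target, with one-sided error of about 5.6% to 18%; an unfavourable gap makes the time test conservative.

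Two stronger readings are tempting and are not supported. The first is that both co-primary results are biased: that needs a prognostic difference that the article does not show, and the primary contrast has not been quantified here. The second is that the false-positive risk for rate could become very large (a 10-point gap at f = 40% would give +2.5 points and about 49% if rate were tested alone). Rate is tested only after time is rejected, so where neither outcome has a true effect, a false rate claim cannot exceed the error of the time test.

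What remains is a threat to validity, with negligible effect on power, that is cheap to close and should be closed before the data are analysed.

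**What to change.** Leave the care rule and the label as they are, and make these changes:

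- Add to the ITT analysis, and to both parts of the primary model, a factor for the number of different randomised stations or teams attending (1, 2, 3 or more). Count them by the station that gave each practitioner their original allocation, because allocation is kept after a move.
- Add a sensitivity analysis restricted to incidents where all attending practitioners share one allocation.
- Report the number of mixed-allocation incidents overall and by region, and the number of multi-station incidents by arm.
- Reconcile the sections on assignment of randomisation group and on blinding with the mixed-attendance rule, stating that the label also depends on who attends.

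The adjustment removes the labelling imbalance for ITT. It does not remove the separate selection created by restricting the primary groups according to pathway use.

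The cost is one covariate, one sensitivity analysis and a few lines of text, with no extra patients. The small downside is data supply: the article says exports hold practitioners and/or stations or teams, so any service that exports only one station per incident must supply the full attending list, preferably before database lock.
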